**Figure 1 figure1:**
[figure not shown]
Trial flowchart. NDI: Neck Disability Index; PNF: proprioceptive neuromuscular facilitation; VAS: Visual Analogue Scale.

### Ethical Considerations

Prior to enrollment, written informed consent will be obtained from all participants by trained research staff, with the consent document clearly outlining the study objectives, procedures, potential benefits and risks, confidentiality measures, and the participant’s right to withdraw at any time without penalty. Participant identities will be anonymized using unique study identifiers, and all data (including clinical records, assessment forms, and biological samples) will be stored on encrypted servers accessible only to authorized research personnel, while publication of results will avoid disclosing identifiable information and comply with the SPIRIT (Standard Protocol Items: Recommendations for Interventional Trials) 2025 guidelines (Multimedia Appendix 1) on data sharing (item 6). An independent Data Safety and Monitoring Board (DSMB) will oversee the trial to ensure participant safety, reviewing AE reports at predefined intervals and potentially recommending trial modifications or termination if unacceptably high risks are identified, with all serious AEs reported to the ethics committee within 24 hours of discovery in accordance with institutional policies. The study protocol has been reviewed and approved by the Regional Ethics Committee of the Affiliated Hospital of Beijing University of Chinese Medicine (approval number: BUCM-2023-078; project number: 2022BZYLL1011).

### Participant Recruitment

Eligible participants include patients diagnosed with NCNP according to Canadian evidence-based guidelines of 2014 for the chiropractic treatment of adults with neck pain [18]. These guidelines define NCNP as follows:

Chronic neck pain lasting for at least 3 months with or without radiation to the upper limbsAbsence of significant structural pathology (fractures, tumors, systemic disease) to exclude serious organic causes requiring urgent medical interventionNonspecific neck pain without a clear underlying pathologyFunctional impairment affecting activities of daily living or work-related tasks

### Diagnostic Responsibility

Two experienced orthopedic specialists (≥10 years of clinical experience in musculoskeletal disorders) will independently review medical histories, physical examination results, and imaging studies (if available) to confirm the diagnosis, reducing interrater variability. Recruitment will be conducted in two ways, offline posting of posters and online posting of information.

### Inclusion Criteria

Participants who meet all the following criteria can be enrolled:

Aged 18-50 years, male or female. This age range is selected to exclude adolescents (immature spinal development) and older adults (higher likelihood of comorbidities, such as osteoarthritis), focusing on a homogeneous population with primary NCNP.The main symptom is neck pain (VAS score≥3 and NDI score≥10), including pain, stiffness, and limitation of movement in the occiput, neck, shoulder, or scapula. These thresholds ensure participants have moderate pain and disability, making them suitable for interventional studies.Physical examination of the cervical spine does not exhibit indications of nerve root compression, which means negative results on the neck distraction test, the Spurling neck compression test, and the Adson test. Excluding radiculopathic pain allows isolation of “nonspecific” neck pain, aligning with the study’s focus.Neck pain continued for at least 3 months. Consistent with the Canadian guidelines’ definition of chronicity, this ensures sufficient time for intervention effects to manifest.No history of shoulder and neck surgery. Prior surgery may alter musculoskeletal anatomy and confound outcomes.Voluntary participation and ability to provide written informed consent. This is mandatory for ethical compliance and participant autonomy.

### Exclusion Criteria

Participants meeting any of the following criteria will be excluded:

Being treated or have been treated in the past 3 months for NCNP with tuina, PNF, or another effective method. This will avoid carryover effects from prior therapies (eg, tuina, PNF) on primary outcomes.Accompanied by compression of nerve roots, the spinal cord, vertebral arteries, sympathetic nerves, etc. These conditions require specialized treatment and belong to specific neck pain subtypes, outside the study’s scope.Localized skin breakdown, skin disease, or skin sensory impairment. This may interfere with treatment delivery (eg, tuina massage) or cause discomfort.Women who are pregnant or lactating. The intervention may cause potential risks to fetal/infant health, and hormonal changes may affect pain perception.Cognitive impairment, sensory aphasia, or severe visual or hearing impairment. This may compromise outcome reporting (eg, VAS scoring) or treatment compliance.Patients who develop neck pain caused by cervical fractures, dislocations, tumors, infections, rheumatoid arthritis, or other specific reasons. The study’s focus is NCNP, as defined by the Canadian guidelines.Patients with a history of severe trauma or tumors. These are high-risk comorbidities that may interact with interventions or affect safety.Pain in more than three areas other than the neck and shoulder area. This suggests widespread pain syndromes (eg, fibromyalgia), which have a different pathophysiology.A combination of serious medical conditions, such as cardiovascular, hematopoietic, and endocrine diseases. This may increase intervention risks or require concomitant medications that interfere with outcomes.

### Dropout Criteria

The dropout criteria are as follows:

The patient quits (poor efficacy or adverse reactions), which respects participants’ rights and ensures data integrity by excluding noncompliant cases.Loss to follow-up, which minimizes missing data bias; participants with ≥50% missing follow-up data will be excluded from the final analysis.Researchers remove the patient (poor compliance, complications, or serious AEs), which ensures safety and protocol adherence (eg, severe AEs require immediate termination).

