The primary outcome measures of this trial are the VAS and NDI scores. The secondary outcome measures are cervical active joint mobility and muscle physical properties. The three groups will be tested before the intervention (baseline), at the fourth week of the intervention, and at the follow-up visit 4 weeks after the end of the intervention. The study design is illustrated in the flowchart in Figure 1.

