#### Statistical Analysis

The intention-to-treat principle will be followed in the primary data analysis with IBM SPSS Statistics for Windows version 27.0 software by statisticians who are blinded to the group allocation. Baseline characteristics will be expressed with descriptive statistics for the groups as the mean (SD). The Kolmogorov-Smirnov test with Lilliefors correction will be performed to analyze all quantitative variables to determine whether they follow a normal distribution. Parametric statistics (Tukey test) or nonparametric statistics (Wilcoxon rank-sum test) will be used for the within- and between-group analyses in accordance with the results of homogeneity and normality analyses. When initial homogeneity and normality of data distribution are found, repeated measures ANOVA and ANOVA with Bonferroni post hoc statistics will be used for within- and between-group analysis. The Friedman test and the Kruskal-Wallis test will be performed when initial homogeneity but not normality of data distribution is found. If initial homogeneity is not found, a linear mixed model will be adjusted for the baseline value. AEs in each group will be documented as percentages for safety assessments using the chi-square test or the Fisher exact test. Statistical significance is defined as *P*<.05, and 95% CIs will be reported.

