## Results

As of the data cutoff date (May 26, 2025), 43 participants were enrolled and randomly assigned to the three treatment groups (PNF group: n=14, 32.6%; tuina group: n=15, 34.9%; combined group: n=14, 32.5%), with recruitment initiated on April 1, 2025, via hospital outpatient clinics (n=45, 65.2%) and online posting (n=24, 34.8%). All enrolled participants have initiated treatment, with an average adherence rate of 92% (measured using session attendance records), and no withdrawals have occurred due to AEs or treatment dissatisfaction. The short-term follow-up (end of intervention) for the first cohort was completed on July 30, 2025, with long-term follow-up (1 month postintervention) to be completed by August 31, 2025. The final analysis is projected to include data of all 69 participants by October 2025, with primary results planned for publication in December 2025.

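### The dropout criteria exclude randomised participants from the final analysis, which contradicts the stated intention-to-treat primary analysis

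*Protocol article*

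**What the plan says.** Under Statistical Analysis: "The intention-to-treat principle will be followed in the primary data analysis".

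Under Dropout Criteria there are three rules:

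- On loss to follow-up: "participants with ≥50% missing follow-up data will be excluded from the final analysis".
- On those who leave by choice: "The patient quits (poor efficacy or adverse reactions), which respects participants’ rights and ensures data integrity by excluding noncompliant cases".
- On removal by the team: "Researchers remove the patient (poor compliance, complications, or serious AEs), which ensures safety and protocol adherence".

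The Study Design section schedules assessments at baseline, "at the fourth week of the intervention, and at the follow-up visit 4 weeks after the end of the intervention". The Results section treats the first of the two post-baseline visits as a follow-up as well: "The short-term follow-up (end of intervention) for the first cohort was completed on July 30, 2025". It calls the second one the long-term follow-up.

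The Abstract and the Results section use the term final analysis for the main analysis and project that it will hold data from all 69 participants.

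**The concern.** Intention-to-treat keeps every randomised participant in the assigned arm. Here one rule removes participants from the analysis because their data are incomplete. A second describes as excluded those who left because treatment failed or harmed them. Both depend on events after randomisation, and the second is tied by its own wording to response and tolerability.

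Two things are at stake. First, the comparison between arms is no longer protected by randomisation for those who remain: if one arm loses more poor responders than another, its remaining mean looks better than it should. Differential loss is conceivable because the combined arm has sessions of about 60 minutes against 30 in the other arms, but the documents do not show that it occurs. Second, valid primary data are thrown away. The end-of-intervention comparison is a stated objective in its own right, yet a week-4 VAS or NDI value would be dropped because a later visit was missed.

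**Working it through.** **Step 1. The statements side by side.** Intention-to-treat is stated for the primary analysis, without qualification. The 50% rule applies to the final analysis, which elsewhere in the article is the main analysis of all 69. It therefore cannot be read as belonging to a per-protocol side analysis, and no other section limits it in that way. The strength of each exclusion differs:

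| Group | What the Dropout Criteria say about analysis |
|---|---|
| At least 50% of follow-up missing | Explicit exclusion from the final analysis |
| Quit for poor efficacy or adverse reactions | Nearly explicit: "ensures data integrity by excluding noncompliant cases" |
| Removed by researchers | Removal stated; analysis set not named |

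**Step 2. What the 50% threshold catches.** Scheduled post-baseline assessments: 2 (Study Design).

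- If both count as follow-ups (Results), one missed visit is 1/2 = 50%, which meets the threshold. Only participants with both visits stay in.
- If only the visit 4 weeks after treatment counts, missing it is 1/1 = 100%. That participant is still excluded, but one who misses week 4 alone stays in.

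A missed week 8 therefore excludes on either reading.

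**Step 3. How many this could be.** The plan's own allowance is 8% dropout with at least 20 evaluable per group: 23 × 0.92 = 21.2, which meets that target. The per-visit missingness m below is an assumption, and both visits are counted as follow-ups. If visits are missed independently, the excluded share is 1 − (1 − m)². If the same people miss both visits, it is m.

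| m | Independent | Of 69 | Same people miss both |
|---|---|---|---|
| 4% | 7.8% | about 5 | 4% |
| 8% | 1 − 0.92² = 15.4% | about 11 | 8% |
| 15% | 27.8% | about 19 | 15% |

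At an independent 8% per visit, 23 × 0.92² = 19.5 per group remain, just under the target of 20.

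**Step 4. Possible shift in the comparison.** Let f be the fraction of an arm excluded and g the amount by which stayers do better than leavers. The full-arm mean is (1 − f) × stayers + f × leavers, so the stayers' mean is too favourable by f × g. The shift between arms A and B is f_A × g_A − f_B × g_B.

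Inputs:

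- f = 0.08 in one arm and 0 in the other. The 8% is the overall dropout allowance under Sample Size Calculation; placing it all in one arm is an assumption.
- g = 1.35 to 2.1 VAS points. This is an assumption. The lower end is the planned difference of 13.5% read on the 0–10 scale. The upper end equals the tuina-versus-sham reduction in the Introduction. Neither measures how leavers differ from stayers.

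Results:

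- 0.08 × 1.35 = 0.11 points; 0.11/1.35 = 8% of the planned difference.
- 0.08 × 2.1 = 0.17 points; 0.17/1.35 = 12%, rounded.
- With equal f and equal g in both arms, the shift is 0.

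**The case against.** Four points can fairly be made against this.

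- **Breadth.** A reader might infer that all three dropout rules remove participants from the analysis, so that the trial is a pure completer analysis. The text does not go that far. For researcher removals the stated purposes are safety and protocol adherence, and the rule can be read as ending treatment only. A reader might also infer that missing either visit always excludes. That depends on counting week 4 as a follow-up, and other sections reserve the term for the period after treatment. Both limits stand.
- **Analysis method.** A reader might argue that repeated measures ANOVA would drop incomplete cases in any case. The article also names a linear mixed model, though only where baseline homogeneity fails, and the handling of missing values may be set out in an analysis plan that is not shown. The point does not need this argument.
- **Size.** The gap between leavers and stayers has no source, and loss in one arm only is the unfavourable case. The Results section reports 92% average adherence and no withdrawals for adverse events or dissatisfaction among the 43 enrolled at the data cutoff. It would go too far to say that randomisation is certainly broken or that a given arm will be flattered. This stands too, although those are early data.
- **Feasibility.** The trial is under way, participants may withdraw at any time, and the calls described under Safety Evaluation ask about the neck condition without naming VAS or NDI. This limits what can be recovered and has to be respected in the fix.

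None of these reconciles the 50% rule, or the wording on those who quit, with intention-to-treat.

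**Conclusion.** The contradiction holds and rests on no numerical assumption. The primary analysis is said to be intention-to-treat, while randomised participants are to be left out of the final analysis for missing follow-up and, in nearly explicit terms, for quitting over poor efficacy or adverse reactions. Researcher removals can be read the same way, but that is inference.

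That a missed week 8 discards a valid week-4 value is firm on either reading of follow-up. That a missed week 4 alone also excludes is firm only if both visits count.

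The bias is conditional on losses, or the outcomes of those lost, differing by arm. The 0.11 to 0.17 point shift illustrates one unfavourable case and does not predict the trial's error. The reason to correct this is that it decides who is in the primary analysis, not the size of that illustration.

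**What to change.** 1. Reword the Dropout Criteria so that they describe leaving treatment and not leaving the analysis. The clinical grounds for stopping need not change for this purpose.
2. Delete the 50% exclusion and the wording on excluding noncompliant cases from the primary analysis.
3. State that all randomised participants are analysed in their assigned arm using all available VAS and NDI data, for example with the linear mixed model already named under Statistical Analysis. Participants with no post-baseline value add little or nothing to such a model, so report their number by arm.
4. Seek VAS and NDI at weeks 4 and 8 from those who stop treatment, unless they withdraw consent for follow-up. Both are self-report, so the questions can be added to the planned contacts. Values not collected from earlier leavers may be unrecoverable and should be reported as such.
5. Report the present exclusions only as a supportive per-protocol or completer analysis.

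The change should be dated and documented before the final analysis. The Discussion already gives VAS reductions by arm, and a population chosen after seeing more results would be hard to defend. The cost is protocol and analysis-plan wording, some analysis work, and a few extra questions per contact.

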### Randomization

The randomization sequence will be generated by a random number generator (IBM SPSS Statistics version 27.0), which will be sent to a therapist in opaque envelopes numbered sequentially. The therapist will sequentially open the envelopes and allocate participants accordingly. Eligible patients will be randomized to the tuina group, the PNF group, or the combined group, with 23 patients in each group.

### Blinding

Outcome assessors, data managers, and the statistician will be blinded in this trial and will not share study information with each other. To preserve masking, only the massage therapists will have access to treatment allocation. The patients will not know the group to which they belong before the intervention. The sequence of randomization will be hidden from both evaluators and patients, and this sequence will be kept by the main researcher throughout the study and will not be available to the rest of the participants involved in the trial.

### Intervention

Participants will receive 4 weeks of treatment, thrice a week, for a total of 12 treatments. All exercises will be performed under the careful supervision of trained professionals. In addition, participants will be required to pass a clinical test to make sure that the consistency of the trial is maintained. It should be emphasized that some other treatments for NCNP during the trial will be forbidden, which includes medication therapy, surgery, drug injections, acupuncture, moxibustion, and physical therapy. If the patients receive any other treatment, these will be recorded at each visit. Health education will be provided to all three groups. Patients will be instructed not to perform any additional exercise at home and to avoid poor posture as much as possible.

#### Group 1: The PNF Group

In this arm of the study, the therapist will administer a two-step protocol for about 30 minutes: step 1 is PNF stretching, and step 2 is PNF plyometrics. PNF stretches last for about 20 minutes. PNF weighted bouncing exercises include 10-15 repetitions per set, with 1-minute rest between sets, 3 sets per day for about 10 minutes.

#### Step 1: PNF Muscle Stretching

The hold-relax-antagonist contraction (HRAC) stretching technique will be used [19]. The stretching is performed as follows: (1) The patient is completely relaxed, and the therapist passively pulls the target muscle for 10 seconds [20]; (2) the patient contracts the target muscle at isometric strength for 6 seconds against the resistance applied by the therapist and then relaxes; (3) the patient actively contracts the antagonist muscle of the target muscle and holds it for 30 seconds after a new range of motion is reached; and (4) starting from this new joint angle reached, the target muscle is passively stretched for 10 seconds again. This process is repeated three to five times. The specific procedure is illustrated in Figure 2.

**Figure 2 figure2:**
[figure not shown]
The HRAC stretching technique: (a) upper trapezius muscle stretching, (b) scapularis muscle stretching, (c) suboccipital muscle group stretching, (d-f) pectoralis major stretching, (g) sternocleidomastoid muscle stretching, (h) pectoralis minor stretching, and (i) obliques muscle stretching. HRAC: hold-relax-antagonist contraction.

### Upper Trapezius Muscle Stretching

To start, the patient is placed in the supine position. The head is rotated to the right as far as possible within the painless range, and then the jaw is tucked in as far as possible. The therapist places their left hand on the patient’s occipital bone, with the fingers facing the ceiling, and the right hand on the patient’s left shoulder. The procedure is as follows:

Step 1: The therapist stretches the patient’s left upper trapezius muscle to its maximum size and holds it for 10 seconds (Figure 2a).Step 2: The patient performs a static antagonistic isometric contraction of the left trapezius muscle for 6 seconds and then relaxes (the head remains in the starting position during relaxation).Step 3: The patient’s head is rotated to the right more deeply, the jaw is tucked in (if possible), and the therapist pulls the patient’s left shoulder down more deeply, causing the antagonist muscle (right trapezius superior fasciculus) to contract for 30 seconds.Step 4: The therapist again holds the patient’s left shoulder in a relaxing stretch to its maximum for 10 seconds. This procedure (target muscle stretch for 10 seconds – target muscle antagonist for 6 seconds – relax – antagonist muscle contraction for 30 seconds – relax – stretch to maximum amplitude for 10 seconds) is repeated for three to five cycles.

### Scapularis Muscle Stretching

To start, the patient sits comfortably in a chair, keeping the back lengthened and closing the jaw so that it is close to the chest. The head is then rotated 45° to the right. The therapist stands behind the patient, placing one hand on the back of the patient’s head and the other hand on the upper part of the left scapula. The procedure is as follows:

Step 1: The therapist first static-stretches the patient’s scapularis muscle for 10 seconds (Figure 2b).Step 2: The therapist then guides the patient to slowly raise their head, neck, and left shoulder, while at the same time applying resistance in order to cause an isometric contraction of the left scapularis muscle for 6 seconds. Throughout this process, the patient should be aware that it is not just the head that is being stretched back but rather the head and neck together.Step 3: After the isometric contraction, the patient relaxes and adjusts their breathing.Step 4: On exhalation, the patient retracts their lower jaw at a greater extent so that it stays close to the chest for 30 seconds and then relaxes.Step 5: The patient stretches again to the maximum extent and holds the position for 10 seconds.

### Suboccipital Muscle Group Stretching

To start, the patient is placed in the supine position, and the therapist holds the patient’s head, with the pads (not the tips) of the fingers under the head so that the occipital bone can be reached. The therapist allows the patient to tuck their lower jaw as close to the throat as possible, trying not to raise the head to bring it closer to the chest but trying to elongate the back of the neck as much as possible. The procedure is as follows:

Step 1: The therapist first static-stretches the patient’s suboccipital muscle for 10 seconds (Figure 2c).Step 2: The patient is then guided to slowly tilt the head back and perform a counterisometric contraction for 6 seconds. If the therapist’s hand slips from the occipital bone, the process starts again, ensuring that the therapist’s hand is in contact with the occipital bone.Step 3: The patient relaxes after the isometric contraction and adjusts their breathing.Step 4: On exhalation, the patient tucks their lower jaw with a greater magnitude in order to get closer to the chest, holding it for 30 seconds, and then relaxes.Step 5: The therapist again stretches the patient’s suboccipital muscle to its maximum magnitude, holding it for 10 seconds.

